### Known drug reactions and interaction with other therapies

Most reported AE associated with low dose or ultra-low dose aldesleukin treatment are of mild or moderate severity (grade 1 or 2)
^22^. The main AE reported in patients or healthy volunteers receiving daily doses between 0.18 × 10
^6^ and 3.0 × 10
^6^ IU/m
^2^ day have been local reactions at injection sites. At the higher doses, considered as “low dose” versus the “ultra-low” doses for the present trial (0.4 × 10
^6^ IU/m
^2^ of aldesleukin per week) flu-like syndromes (fatigue, fever, malaise and arthralgia), have been observed (31%)
^22^. Injection site reactions have been reported in around 30–40% of the treated patients, and they seem to be unrelated to the dose and were not seen for all injections in a given patient. Injection site reactions might be related to the propensity of aldesleukin to form aggregates
^22^.

Not clinically relevant abnormalities in biochemical parameters have associated with use of low doses of aldesleukin. Eosinophilia is dependent on the dose and scheme of administration of aldesleukin. It does not occur in all patients and, for the same individual, it does not occur during after all injections
^23^.

In the T1D participants treated in the DILT1D trial, there was an asymptomatic decrease in eosinophils of approximately 15% at 90 minutes followed by an increase on day 1 that resolved by days 3–4. Six participants developed a transient eosinophilia (count >0.4 × 10
^9^/L)
^23^. Changes in eosinophil count on day 1 was dependent on the additive effects of dose through a model that included both the baseline and dose effects. There was a positive relationship with a higher pre-treatment eosinophil count leading to a greater increase in eosinophils on day 1.

Safety data for ultra-low dose aldesleukin in the paediatric population are available and indicate a low rate of minor AE in this age group
^18^. In a phase 2 paediatric trial, where ultra-low dose aldesleukin (0.1 × 10
^5^ to 0.2 × 10
^6^ IU/m
^2^ three times per week) was administered to 12 paediatric patients after allogeneic hematopoietic stem cell transplantation for 6 and up to 12 weeks, AE were all grade 1 only and included muscle aches, arthralgia, fatigue, nausea and decreased appetite. There was no increased risk of infection or relapse.

Some preliminary data from an ongoing paediatric study were recently included in a review on the safety of low-dose IL-2. They indicated that IL-2 was well tolerated in 18 children (7–12 years old) with T1D who were treated with a dose of 0.25 - 1.0 × 10
^6^ IU per day for a mean duration of more than 6 months
^22^.

More than 13 clinical studies in humans have been completed, including one in healthy volunteers, and others in patients with various conditions: Hepatitis C-induced vasculitis, chronic GvHD, prevention of acute GvHD, T1D, alopecia areata, systemic lupus erythematosus and amyotrophic lateral sclerosis
^13–
30^. Altogether, these studies demonstrated that the increases in Treg number/function were associated with a good tolerance, while an improvement in the clinical outcome was observed in patients with vasculitis, GvHD, alopecia areata and systemic lupus erythematosus. All these studies used Proleukin® (aldesleukin), and the administered doses (by dilution of the formulated Proleukin®) were well below those prescribed for the marketed indications.

The safety of IL-2 is summarized in the aldesleukin SmPC. The doses used in cancer studies are very much higher than those proposed in autoimmune diseases, and the route of administration is most often intravenous. The occurrence of side effects is considerably reduced with the subcutaneous route.

For doses higher than or equal to 10 × 10
^6^ IU/day administered subcutaneously, SAE are observed; with doses lower than or equal to 3 × 10
^6^ IU/ day administered subcutaneously no serious adverse reaction has yet been reported.

**Interactions:** Aldesleukin must be avoided in patients taking antineoplastic agents, interferon-alpha therapy, psychotropic drugs
^38^. Medicinal products with known nephrotoxic, hepatotoxic or cardiotoxic potential should be used with caution. Concomitantly administered glucocorticoids may decrease the activity of aldesleukin and therefore should be avoided
^38^. However, patients who develop life-threatening signs or symptoms may be treated with dexamethasone until toxicity resolves to an acceptable level.

Blood pressure should be monitored in patients on treatment with antihypertensive agents, such as beta-blockers, for potential hypotension risk. Contrast media need to be avoided within 2 weeks after treatment with aldesleukin
^38^. In the event of an acute hypersensitivity reaction to aldesleukin, supportive care will be given to the patient according to local clinical protocols.

### Concomitant treatments

All participants will continue to receive intensive insulin treatment, using either multiple daily insulin injection or insulin pump. The patients’ primary physicians will retain responsibility for their diabetes management, and treatment will be prescribed and administered according to local clinical practice at each site, but the research study team can provide close additional support through interaction by phone between study visits as needed.

During the DBS home collection, short or rapid acting insulin should be avoided until the 60- minute sample has been collected.

## Assessment of safety

Safety will be assessed by frequency, incidence and nature of AE and SAE arising during the study.

### Interim safety review

An interim analysis based on safety measures is planned for the age-based step-down approach. The plan is to expose to treatment firstly six subjects in the age group 12–18 years for a minimum of one month. If after review of the unblinded external safety data, satisfactory safety is established, recruitment will be extended to the younger age group, 6–11 years.

### Expected Adverse Reactions (AR)/Serious dverse reactions (SARs)

All expected ARs are listed in the reference safety information, Section 4.8 of the current, approved SmPC
^38^. This must be used when making a determination as to the expectedness of the AR. If the AR meets the criteria for seriousness, this must be reported following the specific requirements.

The relationship of each AE to the trial medication must be determined by a medically qualified individual according to the following definitions:

a) Related: The adverse event follows a reasonable temporal sequence from trial medication administration. It cannot reasonably be attributed to any other cause.

b) Not Related: The AE is probably produced by the patient’s clinical state or by other modes of therapy administered to the patient.

Expectedness will be determined according to the reference safety information, Section 4.8 of the current, approved SmPC.

All AEs occurring during the trial, from randomisation until 30 days after completion of trial treatment, that are observed by the Investigator or reported by the participants, parent/guardian will be recorded on the CRF, whether or not attributed to trial medication.

Clinicians, during the clinic visit AE review, should at a minimum assess: IMP/placebo injection sites (redness, swelling, nodule, and pain), episodes of high temperature, loss of appetite, diarrhoea, nausea, vomiting, reduced activity, chills, headache, and muscle pain.

The following information will be recorded: description, date of onset and end date, severity, assessment of relatedness to trial medication, other suspect drug or device, and action taken. Follow-up information should be provided as necessary.

The local Principal Investigator (or other delegated member of the study team) will review each AE to assess and document the severity of the impact of the event. The severity of events will be assessed on the following scale: 1 = mild, 2 = moderate, 3 = severe.

It will be left to the Investigator’s clinical judgment to decide whether or not an AE is of sufficient severity to require the patient’s removal from treatment. A participant, or his/her parent/guardian, may also voluntarily withdraw from treatment due to what he or she perceives as an intolerable AE. If either of these occurs, the participant must undergo an end of trial assessment and be given appropriate care under medical supervision until symptoms cease, or the condition becomes stable.

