### Reporting procedures for serious adverse events

All SAEs will be recorded from IMP/placebo administration and until the final trial visit.

All SAEs must be reported on the SAE reporting form, which will be scanned and emailed to the Trial Office within 24 hours of the Site Study Team becoming aware of the event.

The local Investigator will perform initial assessment of SAE causality on the SAE form. All SAEs will be reviewed by the Nominated Person to determine whether the SAE is related and unexpected. Expectedness will be assessed against the reference safety information, Section 4.8 of the current, approved SmPC. SAEs which may be linked to trial procedures and are unexpected will be recorded as Suspected Unexpected Serious Adverse Reactions (SUSARs).

The Trial Office will perform an initial check of the report, request any additional information, and will pass it on to the nominated clinician without delay. It will also be reviewed at the next Data and Safety Monitoring Committee meeting.

AEs considered related to the trial medication as judged by a medically qualified investigator or the nominated clinician for safety review will be followed either until resolution, or the event is considered stable.

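### The two causality categories leave a gap and the SUSAR rule applies a different test, so the same serious event can be classified either way

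*Protocol article*

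**What the plan says.** The section of the protocol article on expected adverse reactions requires a medically qualified person to judge each event's relationship to trial medication by two definitions.

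- Related has two parts. The first is timing: "The adverse event follows a reasonable temporal sequence from trial medication administration". The second is exclusion of alternatives: "It cannot reasonably be attributed to any other cause".
- Not Related reads: "The AE is probably produced by the patient’s clinical state or by other modes of therapy administered to the patient".

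There is no intermediate category and no rule for an event that fits neither.

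*Reporting procedures for serious adverse events* gives the local investigator the initial causality assessment. The Nominated Person then decides whether the event is both related and unexpected. Two sentences later the recording rule is: "SAEs which may be linked to trial procedures and are unexpected will be recorded as Suspected Unexpected Serious Adverse Reactions (SUSARs". The same section has events judged related to the medication followed until they resolve or are stable.

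*Suspected unexpected serious adverse reporting* attaches the consequences. SUSARs go to the competent authority, the ethics committee and every site, within 7 calendar days if fatal or life-threatening and within 15 otherwise. The treatment code is broken for the patient concerned.

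**The concern.** Two categories used to sort every event should be complementary, and these are not. One demands that no other reasonable cause exists; the other demands that another cause is probable. Between them lie events for which the drug is a real candidate and something else is also plausible.

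Such events are easy to imagine here. The effects that the protocol links to low-dose aldesleukin include fever, fatigue, malaise, arthralgia and nausea, which are non-specific. The participants are children and adolescents with newly diagnosed diabetes on intensive insulin. For a serious form of such an event, infection or a glucose disturbance could often be argued as an alternative.

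The SUSAR rule might have settled these cases, but it changes both the threshold (a possible link is enough) and the object (procedures instead of medication). The route a suspected serious drug reaction takes then depends on which sentence the assessor applies.

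**Working it through.** No stated figure is involved, so the check sets the definitions side by side.

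**Step 1: coverage of the two definitions.** Let timing either fit or not fit, and grade the best alternative cause as not reasonable, plausible but not probable, or probable. I read the two sentences under Related as joint requirements. That gives 2 × 3 = 6 combinations.

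| Alternative cause | Timing fits | Timing does not fit |
|---|---|---|
| Not reasonable | Related | neither |
| Plausible, not probable | **neither** | neither |
| Probable | Not Related | Not Related |

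Related covers 1 combination and Not Related covers 2, so 6 − 1 − 2 = 3 are uncovered. These are counts of logical cases, not event frequencies. The cell that matters is the one in bold: the drug is a credible cause, yet the event need not be called related.

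**Step 2: carry events with fitting timing into the SUSAR rule.** Suppose each is serious and unexpected. Test A is the Nominated Person's decision (related and unexpected), with related as defined in the section on expected adverse reactions. Test B is the recording sentence (possibly linked to trial procedures, and unexpected). Procedures may or may not include giving the drug.

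| Alternative cause | Test A | Test B, procedures include the drug | Test B, procedures exclude the drug |
|---|---|---|---|
| Not reasonable | SUSAR | SUSAR | not a SUSAR through the drug |
| Plausible, not probable | not met | SUSAR | not a SUSAR through the drug |
| Probable | not met | can be a SUSAR, since a probable alternative does not rule out a possible link | not a SUSAR through the drug |

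Under neither reading of procedures do tests A and B agree in every row. On the broad reading they part in the second row and can part in the third. On the narrow reading they part in the first row, where a clear drug reaction would not qualify through the drug.

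**Step 3: what depends on the result.**

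- Dependent: SUSAR status, the code break for that patient, the 7- or 15-day reports, and the follow-up attached to related events.
- Not dependent: recording of adverse events, which is done whatever the attribution; reporting of every serious event to the Trial Office within 24 hours; review at the next Data and Safety Monitoring Committee meeting; the interim safety review on unblinded data; and the comparison of event incidence between arms in *Description of statistical methods*.

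**The case against.** The best counter-argument is that trial procedures already include the drug. *Trial procedures* refers the reader to Table 3 for the study procedures, and that table lists aldesleukin or placebo administration. The R in SUSAR also stands for reaction, and the later SUSAR section speaks of the investigational product. On that reading the recording sentence is a low-threshold trigger that would catch the middle group. I accept this as the likelier intention, because the narrow reading would leave out plain drug reactions. It does not resolve the point: it makes the clash of thresholds sharper, since the preceding decision still turns on a definition that the middle group fails.

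It is also fair to say that the text leaves a gap and not a default. A merely arguable alternative does not make an event Not Related either. A reader might infer a systematic bias towards not related, and so a falsely reassuring safety result. The documents do not support that. *Assessment of safety* bases safety on the frequency, incidence and nature of events, and relatedness does not enter the comparison of incidence.

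A reader might also infer that expectedness is set wrongly. The rule is "Expectedness will be determined according to the reference safety information, Section 4.8 of the current, approved SmPC", the licensed use is at much higher doses in adults with cancer, and the protocol says that at or below 3 × 10^6 IU/day "administered subcutaneously no serious adverse reaction has yet been reported". That inference goes too far. Section 4.8 is not among the documents, so its serious terms cannot be checked. The sentence on low doses reports past experience and sets no rule on expectedness, so using the product label as the reference contradicts nothing in the article.

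Finally, follow-up is partly protected by another route: *Early discontinuation/withdrawal of participants* requires follow-up of events that lead to withdrawal, whatever their attribution.

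**Conclusion.** The point holds in a limited form. The causality categories are not complementary, and the two sentences that decide SUSAR status use different thresholds and, on their face, different objects. A serious event with fitting timing and a plausible but not probable alternative cause can be classed either way by assessors who both comply with the text.

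The effect is confined to SUSAR classification, with its unblinding and expedited reports, and to follow-up of related events. It cannot be sized, because the document states no expected rate of serious events and nothing allows a misclassification rate to be assumed.

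The conclusion rests on reading the two sentences under Related as joint requirements, and on taking the article's wording as what sites and the Nominated Person apply. It does not rest on the content of the product label.

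**What to change.** Reconcile the two sections around one complementary definition. Related would mean a reasonable possibility that the trial medication caused or contributed to the event; Not Related would mean no such possibility. Reword the SUSAR sentence so that it refers to the trial medication and uses that same threshold, in agreement with the Nominated Person's decision just before it.

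The cost is a short amendment to the safety-reporting text and a memo to sites. The downside is a few more events classed as related and possibly more expedited reports, each with a code break. No analysis or sample-size text needs to change.

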### Reporting procedures for serious adverse events

All SAEs will be recorded from IMP/placebo administration and until the final trial visit.

All SAEs must be reported on the SAE reporting form, which will be scanned and emailed to the Trial Office within 24 hours of the Site Study Team becoming aware of the event.

The local Investigator will perform initial assessment of SAE causality on the SAE form. All SAEs will be reviewed by the Nominated Person to determine whether the SAE is related and unexpected. Expectedness will be assessed against the reference safety information, Section 4.8 of the current, approved SmPC. SAEs which may be linked to trial procedures and are unexpected will be recorded as Suspected Unexpected Serious Adverse Reactions (SUSARs).

The Trial Office will perform an initial check of the report, request any additional information, and will pass it on to the nominated clinician without delay. It will also be reviewed at the next Data and Safety Monitoring Committee meeting.

AEs considered related to the trial medication as judged by a medically qualified investigator or the nominated clinician for safety review will be followed either until resolution, or the event is considered stable.

### Events exempt from immediate reporting as serious adverse events

Hospitalisation for elective procedures planned prior to study entry, which have not worsened, do not constitute a SAE.

### Suspected unexpected serious adverse reporting

All SUSARs will be reported by the Chief Investigator to the relevant Competent Authority and to the Research Ethics Committee, and to each participating site, and other parties as applicable. For fatal and life-threatening SUSARs, this will be done no later than 7 calendar days after the Sponsor or delegate is first aware of the reaction. Any additional relevant information will be reported within 8 calendar days of the initial report. All other SUSARs will be reported within 15 calendar days. Treatment codes will be un-blinded for specific patients.

Principal Investigators will be informed of all SUSARs for the relevant IMP for all studies with the same Sponsor, whether or not the event occurred in the current trial.

### Development safety update reports

The Chief Investigator will submit (in addition to the expedited reporting above) Development Safety Update Reports once a year throughout the clinical trial, or on request, to the Competent Authority (Medicines and Healthcare products Regulatory Agency (MHRA) in the UK), Ethics Committee, HRA (where required), Host NHS Trust and Sponsor.

### Pregnancy reporting

Pregnancy testing will be performed, where appropriate, at the beginning and during the trial period up to the last visit while on treatment. All subjects and their parents will be informed of the potential risks and the need for trial patients to use contraception, if sexually active, for the duration of treatment and for 30 days afterwards.

Guidance is in place to deal with any pregnancy, including immediate unblinding and comprehensive independent counselling as to the advisability of continuing the pregnancy.

Participants will be instructed to notify the Investigator immediately if they become pregnant and will be advised to discontinue any study medication immediately. This would be grounds for immediate unblinding to ascertain whether conception had occurred during treatment with placebo or the active drug.

All pregnancies within the trial (either the trial participants or the participant’s partner) should be reported to the Trial Office using the relevant Pregnancy Reporting Form (copies provided in the Investigator Site File) within 24 hours of becoming aware of the event. Pregnancy is not considered an AE unless a negative or consequential outcome is recorded for the mother and/or child/foetus. The outcome of the pregnancy should be recorded and followed up for congenital abnormality or birth defect, at which point it would fall within the definition of “serious”.

## Statistics

### Description of statistical methods

Full details of the statistical analysis will be detailed in a separate statistical analysis plan (SAP) which will be drafted early in the trial and finalized prior to the primary analysis data lock.

Descriptive statistics will be used to describe the demographics between the treatment groups. The primary outcome is change in DBS C-peptide (slopes) during the 6-month treatment period. This will be analysed using Analysis of Covariance (ANCOVA) with adjustment for stratification factors (site, age group) and baseline C-peptide values. Between group differences with corresponding 95% confidence intervals will be reported. If not normally distributed, non-parametric methods will be used with no adjustment (for example the Mann-Whitney Test or Kruskal-Wallis test).

Standard statistical tests will be used to compare the actively treated group with the placebo group (t test, Mann Whitney U-test, analysis of covariance, chi square test), with P values below 0.05 indicating significance.

The incidences of adverse events will be reported and, where appropriate, the two groups will be compared with the use of a logistic regression model.

Analyses will be undertaken on an intent to treat population (all patients analysed as randomised) with sensitivity analyses undertaken to explore deviations from the protocol and compliance with treatment.

An interim analysis based on safety measures is planned for the age-based step-down approach. The plan is to expose to treatment firstly six participants in the age group 12–18 years for a minimum of one month. If after review of the unblinded external safety data and satisfactory safety is established, recruitment will be extended to the younger age group, 6–11 years.

Stata (StataCorp LP) or other appropriate validated statistical software will be used for analysis.

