### Trial participants

The trial population will be represented by 45 children and adolescents, aged 6–18 years, newly diagnosed with T1D. Study participants will be divided in two groups: A (age 12–18 years) and B (age 6–11 years) and recruitment will start with group A. We expect to recruit a minimum of 12 participants in each of the two age groups 12–18 years and 6–11 years. Subjects will be randomised in a 2:1 ratio to aldesleukin or placebo.

After 6 participants from group A have completed a minimum of one month of therapy, there will be a review of safety and efficacy data by the Data and Safety Monitoring Committee and, if no adverse safety signal is observed the recruitment will be widened to include those aged 6–11 years.

Potential participants will be identified from the clinic lists and patient notes at the participating sites. This will be done by the clinical care team.

Infrastructure including several established paediatric clinical sites which are part of the
Type 1 Diabetes UK Immunotherapy Consortium and
ADDRESS-2 will be used to identify and refer potential participants for ITAD.

Information about ITAD will be posted on the Type 1 Diabetes UK Immunotherapy Consortium and ADDRESS-2 websites along with contact forms so that patients visiting these websites can register an interest in hearing more about the study. The Type 1 Diabetes UK Immunotherapy Consortium/ADDRESS-2 coordination team will refer these patients to the study team at one of the participating research sites for ITAD.

Potential participants will be provided with a verbal explanation of the study and written information sheets. Once they have been given sufficient time to consider their participation in the trial, the participants/parents will be asked to provide written informed consent and their assent to the study.

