### Randomisation and blinding

Consented participants will be randomly assigned in a 2:1 ratio, to receive treatment with the active drug (aldesleukin) or placebo using a centralised randomisation service, Registration/Randomisation and Management of Product (RRAMP), provided by the Oxford Clinical Trials Research Unit. Randomisation will be computer generated using a non-deterministic minimisation algorithm to ensure treatment concealment and balanced allocation across the two treatment groups for site and by age group. The service may be accessed via the secure randomisation
website (24 hours/7 days a week).

The patient, local investigator and all study and project management staff will be blinded as to treatment allocation. The statistician will have access to the unblinded code. The site pharmacist will have access to the treatment allocation in order to make up the active drug/placebo.

The RRAMP provides a facility for emergency unblinding of treatment allocation which can be accessed by the local principal investigator. All emergency unbinding will be at the discretion of the local investigators, when clinically indicated for the safety of the patient. Investigators should refer to the standard operating procedures (SOP) for the emergency unblinding procedure provided in the Investigator Site File. Non-emergency unblinding can be requested via the RRAMP system, and will require approval by the Chief Investigator.

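### If the data look non-normal, the primary ANCOVA is replaced by an unadjusted rank test, so the effect measure depends on the data and the minimisation factors and baseline C-peptide drop out

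*Protocol article*

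**What the plan says.** Under Description of statistical methods, the protocol article defines the outcome: "The primary outcome is change in DBS C-peptide (slopes) during the 6-month treatment period". The main analysis follows: "This will be analysed using Analysis of Covariance (ANCOVA) with adjustment for stratification factors (site, age group) and baseline C-peptide values". So does the form of the result: "Between group differences with corresponding 95% confidence intervals will be reported". The next sentence sets the fallback: "If not normally distributed, non-parametric methods will be used with no adjustment (for example the Mann-Whitney Test or Kruskal-Wallis test".

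Under Randomisation and blinding, allocation uses a "non-deterministic minimisation algorithm to ensure treatment concealment and balanced allocation across the two treatment groups for site and by age group". The two factors balanced by design are therefore two of the three covariates that the fallback removes. Allocation is 2:1 (Trial participants), and significance is set "with P values below 0.05 indicating significance".

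The same statistics section leaves full details to a statistical analysis plan, to be finalised before the primary data lock. The removal of adjustment, however, is already fixed in the protocol.

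**The concern.** Three things follow from the fallback sentence.

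- **The effect measure changes with the data.** Table 1 defines the primary outcome as a difference in slopes between the groups, and the Power calculation sizes the trial on a slope difference of 0.53. A Mann-Whitney test addresses a different hypothesis and does not estimate an adjusted mean slope difference. Kruskal-Wallis adds nothing with two arms.
- **The analysis stops matching the design.** Minimisation makes the arms more alike on site and age group than simple randomisation would. An unadjusted test still counts the variation due to those factors as noise. If they are prognostic, its P values are too large.
- **Baseline C-peptide is dropped.** It is not a minimisation factor, so omitting it does not bias the type I error. It may cost precision.

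At stake are the interpretability of the primary result and, in some settings, power. The choice would rest on a normality judgement with 36 to 45 participants, only 12 to 15 of them on placebo. Randomisation and blinding also gives the statistician the unblinded code.

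**Working it through.** **1. The plan's own figure.** Inputs from the Power calculation: 24 active and 12 placebo, slope difference 0.53, SD 0.523, equal-variance two-sample t-test. Two-sided alpha of 0.05 is assumed.

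- Standard error: 0.523 × √(1/24 + 1/12) = 0.523 × 0.3536 = 0.1849.
- Noncentrality: 0.53 / 0.1849 = 2.87, on 34 degrees of freedom.
- Power: 79.5% by the noncentral t; 81.8% by the normal approximation.

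The stated 80% reproduces. It rests on an unadjusted test, so it does not depend on the covariates.

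**2. Why an unadjusted test is conservative after minimisation.** Let R² be the share of slope variance explained by site and age group. The document does not give it. With perfect balance and normal errors, the real variance of the mean difference is (1 − R²) times what the unadjusted test supposes. The type I error is then about 2Φ(−1.96/√(1 − R²)):

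- R² = 0.2: 1.96/0.894 = 2.19, giving 2.8%.
- R² = 0.4: 1.96/0.775 = 2.53, giving 1.1%.

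Simulated rank tests agree. With 45 participants, 2:1 minimisation on six assumed sites and two age groups, and normal errors, type I error was 3.0% and 1.3%.

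**3. Skewed errors, where the switch would operate.** The design is as in step 2, with covariates explaining an assumed 20–60% of variance.

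| Analysis | Type I error | Power |
|---|---|---|
| Unadjusted rank test | about 0.2–2.5% | about 91–98% |
| Rank ANCOVA, same covariates | about 4–6% | about 97–99% |
| ANCOVA | about 4–6% | see step 4 |

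A separate run of this design, with log-normal errors and newly drawn site effects, gave a rank-test type I error of 0.7% to 3.3%. The direction is the same. The exact values depend on the assumed site effects and skew.

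**4. The switching rule against always using ANCOVA.** The protocol names no trigger, so Shapiro-Wilk on the residuals at 0.05 is assumed. Here there are 24 against 12 participants, one covariate, no minimisation and 6,000 replicates per cell. Skewed errors are log-normal with log-SD 0.75.

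| Errors | R² | ANCOVA power | Rank test power | Switching rule power | Switch made |
|---|---|---|---|---|---|
| Normal | 0 | 78.5% | 77.1% | 78.6% | 5.2% |
| Normal | 0.25 | 89.0% | 76.7% | 88.5% | 4.8% |
| Normal | 0.50 | 97.7% | 76.5% | 96.7% | 4.9% |
| Skewed | 0 | 81.2% | 94.0% | 94.1% | 92.5% |
| Skewed | 0.25 | 88.3% | 88.9% | 89.4% | 92.6% |
| Skewed | 0.50 | 94.9% | 83.9% | 84.8% | 93.0% |

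The rule's type I error was 4.6% to 5.4% throughout. With normal errors it costs less than 1 point of power, because the switch is rare. With skewed errors it gains about 13 points at R² = 0, is roughly level at 0.25, and loses about 10 points at 0.50.

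**The case against.** The strongest defence is that the fallback does little measurable harm and sometimes helps. In a simulation of the switching rule with 45 minimised participants, only site and age group prognostic, and R² of 0, 0.2 and 0.4, its power was 95.3%, 93.9% and 95.1% under log-normal errors (sigma 0.6). ANCOVA had 85.9%, 89.1% and 95.1%. With normal errors the rule lost at most 0.4 points. This stands, and it rules out several stronger readings that a reader might infer:

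- **That the rank test is always less powerful than ANCOVA.** It is not. The large losses occur with normal errors, where a normality check would rarely trigger the switch, or with skew and strongly prognostic covariates.
- **That the switch inflates false positives.** The simulations show error near or below 5%.
- **That the trial is undersized as a result.** The sample size rests on an unadjusted t-test.
- **That normality is to be judged on the raw outcome.** The sentence names neither slopes nor residuals. That detail and the trigger may properly sit in the analysis plan, and once a trigger is fixed there is one primary P value.
- **That no estimate would remain.** The promise of a between-group difference with 95% CI is not withdrawn, and a Hodges-Lehmann shift could accompany the rank test. It would be unadjusted.

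The defence does not answer the main point. The protocol itself prescribes analysis without adjustment, and an adjusted rank analysis would deal with the same skew while respecting the design.

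**Conclusion.** The point holds as a should-fix. The protocol lets a look at the data replace an adjusted slope difference with an unadjusted rank comparison, and so drops site, age group and baseline C-peptide.

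If those covariates are prognostic, the unadjusted test after minimisation is conservative: about 0.2–2.5% type I error under skew. It has less power than an adjusted rank analysis: about 91–98% against 97–99%. Against ordinary ANCOVA the comparison goes either way.

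These sizes rest on assumptions that the document does not supply: R² of 20–60%, six sites (the stated minimum), log-normal skew and, for the switching rule, a Shapiro-Wilk trigger. The change of effect measure and the loss of adjustment follow from the text alone.

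**What to change.** Delete the switch, including the words that remove adjustment, and carry the change into the analysis plan:

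- Keep the covariate-adjusted slope difference with 95% CI as the single primary analysis, whatever the distribution.
- Fix any transformation of C-peptide in advance, or decide it on blinded pooled data.
- Handle non-normal residuals with one prespecified adjusted sensitivity analysis: rank ANCOVA with the same covariates, a bootstrap confidence interval, or a re-randomisation test that follows the minimisation. An unadjusted rank test can be added as supportive.

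The cost is a sentence in the protocol and analysis plan and one more sensitivity analysis. There is a real downside: if residuals are strongly skewed and the covariates explain little, ANCOVA has less power than the rank test (81.2% against 94.0% in the R² = 0 cell above). A transformation chosen in advance may recover some of this. The article reports the trial as still recruiting and the analysis plan as due before data lock, so at that stage the change could be made without compromising the trial.
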